**Resting phase**
Duration: ≥3 minutes (following equipment set-up)Resting measurements recorded during the last minute of this phase
**Warm-up phase**
Duration: 3 minutes following resting phaseWarm-up at an equivalent of 20 watts and at a pedaling rate of 60±5 revolutions per minute
**Incremental phase**
Duration: 8 to 12 minutesWork rate: start at 20 watts and increase by 10 to 15 watts per minute (ramp)Pedaling rate: 60±5 revolutions per minute (stop test if individual falls under 50 revolutions per minute)
**Recovery phase**
Total duration: 5 minutesActive phase (pedaling at 20 watts) for 2 minutes, followed by passive phase (quiet sitting) for 3 minutes
**Monitoring**
Continuous: breath-by-breath gas analysis, electrocardiography, peripheral oxygen saturation (stop test if pulsed oxygen saturation ≤80% with symptoms, such as dizziness, nausea, etc)During the last minute of the unloaded phase, every 2 minutes during the incremental phase, immediately at completion, and at 5 minutes of the recovery phase: blood pressure, dyspnea (/10), and leg fatigue (/10)Pre- and postincremental phase (Québec only): inspiratory capacity

To address current international recommendations that require the test to be repeated twice, the first laboratory visit will end with a familiarization trial of the 6MWT for individuals who have not done the test during the previous 12 months (the 6MWT is routinely conducted during medical follow-ups in the centers in this study) [36,37]. Data from this familiarization trial will not be recorded (although vital signs will be monitored for safety).

#### Second Laboratory Visit

During the second laboratory visit, spirometry will be repeated to ensure the stability of the participants’ health state (particularly relevant for individuals with COPD). Thereafter, the 6MST and 6MWT will be performed in a randomized order, separated by a rest period of at least 30 minutes.

The 6MWT will be performed in a leveled, unobstructed corridor in accordance with current recommendations [36,37]. Briefly, the 30-meter testing area will be marked at both extremities with brightly colored cones. Standardized instructions will be given before beginning the test, and standardized encouragements will be provided every minute during (see Textbox 3 for instructions in French used in this study) [36]. The total distance traveled will be collected to the nearest meter. Dyspnea, leg fatigue, and cardiorespiratory responses will be collected as described previously.

Standardized instructions and encouragements during the 6-minute walk test. See Multimedia Appendix 2 for the English version.
**Standardized instructions in French**
Le but de ce test est de marcher la plus grande distance possible pendant 6 minutes. Vous devrez réaliser des allers-retours dans ce couloir. Six minutes, c’est une longue durée, vous risquez de vous essouffler et de vous fatiguer. Vous pouvez choisir de ralentir ou d’arrêter, si nécessaire. Vous pouvez vous appuyer contre le mur pour vous reposer, mais recommencer la marche dès que possible.Vous ferez des allers-retours en contournant les cônes orange. Vous devriez faire des virages rapides afin de poursuivre dans la direction opposée sans hésitation. Je vais vous montrer comment faire le virage, regardez-moi. (Démonstration)Êtes-vous prêts à faire le test? Je vais compter le nombre d’aller-retour que vous faites et je vous dirai la durée restante toutes les minutes. Rappelez-vous, l’objectif du test est de marcher la plus grande distance possible pendant 6 minutes, mais vous ne devez pas courir. Je vais compter à trois et dire « GO ». Partez lorsque je dis « GO ».
**Standardized encouragements in French**
C’est bien. Il vous reste 5 minutes.Continuez comme ça. Il vous reste 4 minutes.C’est bien. Vous avez fait la moitié.Continuez comme ça. Il vous reste seulement 2 minutes.C’est bien. Il vous reste seulement 1 minute.

The 6MST will be performed in accordance with the original description [16]. The test consists of taking the maximum number of steps on a stepper in 6 minutes. One step is counted for each complete flexion-to-extension movement of a lower extremity. The stepper used will be standardized and identical for all participants (Zinnor Mini Multifunctional Fitness Stepper [Zinnor] in Québec and Athletic Go Sport in France). Participants will be able to lightly touch a stable surface (ie, a wall) for balance, if needed. Participants will be allotted a 2-minute familiarization period, followed by rest (≥3 minutes seated), then will begin the test. Standardized validated instructions and encouragements, adapted from those of the 6MWT, will be provided (Textbox 4) [16,38]. Evaluators will ensure that complete lower extremity extension is reached during every step. The total number of steps will be automatically provided by the stepper. Dyspnea, leg fatigue, and cardiorespiratory responses will be collected as described previously.

Standardized instructions and encouragements during the 6-minute stepper test. See Multimedia Appendix 3 for the English version.

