### Participants and Inclusion and Exclusion Criteria

A quota sampling method, based on disease and sex (ie, 1:1), will be used. All sample sizes were calculated a priori with an open-source calculator available on the internet or SPSS (IBM) [23]. Inclusion and exclusion criteria are summarized in Textbox 1.

Inclusion and exclusion criteria.

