**Exclusion criteria**
Interstitial lung disease associated with connective tissue disease and sarcoidosis (often accompanied by multisystemic effects)Unstable or severe cardiac conditionInvalidating rheumatologic or neurologic conditionWeight exceeding maximal limits of exercise equipment (eg, 130 kg for the stepper)Any other physical or medical condition limiting or contraindicating exercise testingSimultaneous participation in another study requiring changes in medicationRecent pulmonary rehabilitation (≤1 year, potential learning bias for the 6-minute walk test and the 6-minute stepper test)For study 1 only: use of oxygen therapy (unable to provide oxygen therapy during testing due to limitation of gas exchange analysis equipment)For study 2 only: participation in study 1

For study 1, a mean difference of 0.28±0.32 L/min in maximal oxygen uptake between the 6MST and CPET was assumed, based on previous studies between the 6MWT and CPET [22,24]. To detect a difference of this amplitude with a paired sample *t* test, assuming a power of 80%, an α level of .05, and a dropout rate of 15%, 15 participants are needed. Fifteen individuals of each disease population (ie, COPD, n=15; ILD, n=15) will be included for a total sample of 30 participants (Québec, n=15; France, n=15), as cardiorespiratory responses to exercise are different among these populations [25].

For study 2, a minimal acceptable intraclass correlation coefficient of 0.5, and an expected intraclass correlation coefficient of 0.75, were assumed for the test-retest reliability of the 6MST. Assuming a power of 80%, an α level of .05, and a dropout rate of 15%, 52 participants (Québec, n=26; France; n=26) will be recruited. This calculated sample was taken as a whole, as test-retest reliability is not expected to be influenced by the type of respiratory disease.

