#### First Trial

The first trial of the 6MST (familiarization trial) will be conducted at the participant’s home with the therapist present. Preceding this trial, the Short Physical Performance Battery will be performed to obtain a general assessment of lower limb function [39].

The 6MST will be performed using a standardized portable stepper (same as in study 1) and following the same protocol as in study 1, including the 2-minute pretest warm-up period. However, full cardiorespiratory responses will not be measured. Instead, an oximeter (Nonin) will be used to monitor heart rate and SpO_2_ continuously. Blood pressure, dyspnea, and perceived exertion will be measured pre*-* and posttest using the modified Borg scale (/10). For individuals on home oxygen therapy, oxygen flows will be titrated if SpO_2_ falls below 88% during the test, with the aim of maintaining SpO_2_ between 88% and 92%, while always respecting the flow limits of the prescribing physician’s parameters. As in study 1, the test will be terminated if blood oxygen saturation falls to ≤80% accompanied by symptoms of hypoxia (such as dizziness, nausea, etc).

All adverse events will be recorded and graded according to the Common Terminology Criteria for Adverse Events, version 5 (United States Department of Health and Human Services), progressing from mild (1) to lethal (5) [40]. Textbox 5 presents the standardized grading used in this study. Adverse events are defined as any event that leads to (or could potentially lead to) prejudice to the participant or that inhibits the completion of the test. Examples include dyspnea, dizziness or nausea, close-call or fall events, musculoskeletal pain, chest pain, syncope, etc.

Classification of adverse events based on the Common Terminology Criteria for Adverse Events, version 5.

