### Potential Challenges and Appropriate Mitigation Strategies

Certain potential changes were foreseen and the following mediation strategies will be put into place:

Changes in a participant’s health status during the study could introduce bias in the results of repeated measures. To help reduce this risk, repeated testing conducted in the laboratory will be preceded by spirometry to ensure stability in health status. For testing conducted in the home-based settings, signs and symptoms of exacerbations will be collected before each repeated testing.The steppers used in this study use hydraulic pistons to simulate the stepping movements. The resistance provided by the pistons is greater when the fluid inside them is cold and decreases progressively with use as the pistons heat. To avoid inducing a potential bias during repeated tests, a standardized 2-minute warm-up (familiarization) will be conducted followed by a standardized 3 minutes of rest before initiating the test trial. Participants will also be instructed not to use the stepper device other than when instructed to do so during testing.Some participants may have trouble maintaining balance during the 6MST. Participants are allowed to touch a wall or other stable surface to assist in maintaining balance. Nevertheless, for home-based testing in the absence of the therapist (ie, videoconferencing), a third person (eg, family member) will be present to ensure safety. This person will also be instructed on how to react in case of emergency.

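### The stepper is called identical for all participants, yet each country uses a different model; a difference in counts between models would bias the pooled step-count ICC and correlations

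*Protocol article*

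**What the plan says.** The 6MST description (Protocol article, Second Laboratory Visit) reads: "The stepper used will be standardized and identical for all participants (Zinnor Mini Multifunctional Fitness Stepper [Zinnor] in Québec and Athletic Go Sport", the second model being the one used in France. The same paragraph adds: "The total number of steps will be automatically provided by the stepper". Study 2 carries both models over. Under First Trial: "The 6MST will be performed using a standardized portable stepper (same as in study 1".

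Participants and Inclusion and Exclusion Criteria fixes the country split at 15 and 15 in study 1 and 26 and 26 in study 2. On the study 2 sample size it says: "This calculated sample was taken as a whole, as test-retest reliability is not expected to be influenced by the type of respiratory disease". That reason concerns disease; it does not mention country or stepper model.

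Data Preparation and Analysis describes, for study 2, a paired t test, Bland-Altman limits and intraclass correlations for trial 2 against trial 3. For study 1 it adds Pearson correlations of step count with peak oxygen consumption and heart rate. No country or stepper term is described for either.

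Potential Challenges and Appropriate Mitigation Strategies treats the device as a possible source of bias: "The steppers used in this study use hydraulic pistons to simulate the stepping movements", and "The resistance provided by the pistons is greater when the fluid inside them is cold and decreases progressively with use as the pistons heat". The remedies given there (warm-up, rest, no use outside testing) address heating within one device, not a difference between models.

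**The concern.** The sentence contradicts itself about the instrument being validated. Every Québec participant uses one model and every French participant the other, so no comparison in the data can separate device from country.

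The step count depends on the piston resistance and the built-in counter, so two models could give different mean counts at the same exercise capacity. In a pooled ICC such a gap is added to the variance between people and looks like better reliability. The reason given for treating the sample as one group concerns test-retest error, but an ICC also rises with the spread between participants.

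At stake is the reliability band reported for objective 2, whose hypothesis is a good ICC, and the size of the study 1 step-count correlations.

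**Working it through.** **Plan's own figure.** The study 2 inputs are a minimum ICC of 0.5, an expected ICC of 0.75, 80% power, alpha .05 and 15% dropout. With two trials (k = 2) the standard ICC formula is n = 1 + 2k(z_alpha + z_beta)² / [(k − 1)(ln C)²], where C = (1 + 2 × 1)/(1 + 2 × 3) = 3/7. Two-sided alpha gives 44.7, hence 45. Then 45 × 1.15 gives 52 and 45/0.85 gives 53. The stated 52 reproduces, so the sample size itself is not in question.

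**Effect of an offset on the ICC.** Let rho be the within-country ICC and D the country difference in mean steps, in within-country SDs of a single test. With equal country sizes the offset adds D²/4 to the between-participant variance:

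pooled ICC = (rho + D²/4)/(1 + D²/4)

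| True ICC | D = 0.5 | D = 1 | D = 1.5 | D = 2 |
|---|---|---|---|---|
| 0.50 | 0.53 | 0.60 | 0.68 | 0.75 |
| 0.70 | 0.72 | 0.76 | 0.81 | 0.85 |
| 0.75 | 0.76 | 0.80 | 0.84 | 0.875 |

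For example, at D = 1: (0.70 + 0.25)/1.25 = 0.76, which moves a value from the protocol's moderate band (0.51-0.75) to its good band (0.76-0.9).

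**Plausible size of D.** The article gives neither a between-model difference nor an SD of steps. Its only yardstick is the minimally important difference of 40 steps (Background). Assuming an SD of 80 to 150 steps:

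- 40 steps is D = 0.5 down to 0.27. A true 0.50 becomes 0.529 to 0.509, and a true 0.75 becomes 0.765 to 0.754. The rise is about 0.004 to 0.03.
- 80 steps is D = 1 down to 0.53. A true 0.50 becomes 0.60 to 0.533, and a true 0.75 becomes 0.80 to 0.767.

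**Check by simulation.** With 22 per country (52 less 15%), 8,000 runs and a true ICC of 0.50, the mean pooled ICC was 0.49, 0.52, 0.59 and 0.68 at D = 0, 0.5, 1 and 1.5. After centring by country it stayed at 0.49 throughout. At a true ICC of 0.75 the country-centred mean stayed at 0.74, and the power to exceed 0.50 (one-sided 0.05) was 86-87%, against 87% for the pooled analysis with no offset. The adjustment therefore costs almost no power.

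**Study 1 correlations.** Let g be the country difference in the other variable, in SDs:

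pooled r = (r + Dg/4)/√[(1 + D²/4)(1 + g²/4)]

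The article's figure for steps against peak oxygen consumption is r = 0.39 (Background).

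- g = 0: 0.378 at D = 0.5, and 0.39/√1.25 = 0.349 at D = 1.
- g = 0.5 in the same direction as the step offset, D = 1: (0.39 + 0.125)/√(1.25 × 1.0625) = 0.447.
- g = 0.5 in the opposite direction, D = 1: (0.39 − 0.125)/√(1.25 × 1.0625) = 0.230.

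The value g = 0.5 is assumed. The gas analysers also differ by country (Maximal Cardiopulmonary Exercise Testing), so g = 0 cannot be taken for granted.

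**What is not affected.** Each participant stays on one country's model, so a constant offset cancels in the trial 2 minus trial 3 difference. The paired t test and Bland-Altman limits for steps are not biased by it.

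**The case against.** The strongest reply is that nothing in the article shows that the two models count differently. That stands. A reader might infer that the pooled ICC is inflated; the document supports only that it would be if a net offset exists. An opposing difference in case mix between countries could even cancel a device offset. At the one scale the article offers, 40 steps, the effect is small under the assumed SDs.

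A reader might also infer that device differences could carry the ICC past a formal test against 0.50. The value 0.5 is a planning input; Data Preparation and Analysis interprets the ICC in descriptive bands and states no such test.

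The missing country term is not a fault in itself, because an analysis plan that is not shown may contain one, and the remark about taking the sample as a whole concerns sample size. But no analysis plan can correct the false statement that the stepper is identical for everyone.

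The ICC is not the only reliability measure, since the limits of agreement already show within-person error in steps. In study 1 the step-count correlations are additional analyses, and the sample size rests on a paired oxygen-uptake difference. Both points stand and limit the damage.

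Finally, one might want a disease term in the ICC model, or quotas crossed with site, given "A quota sampling method, based on disease and sex (ie, 1:1), will be used". Neither follows from the device argument. A disease term would remove genuine spread in the mixed population under study, and the article does not say whether the quotas apply within site.

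**Conclusion.** The contradiction is certain: one sentence claims a single identical stepper and names two, and study 2 inherits both. Device is fully confounded with country.

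The bias is conditional on an offset D that the article neither gives nor rules out. It is slight for D up to about 0.5 (at most about 0.03 on the ICC for true values of 0.50 or above) and material from about D = 1, where a true 0.70 would be reported as 0.76. Study 1 step-count correlations could be attenuated, or shifted either way if oxygen uptake also differs by country. These figures assume equal country sizes, equal within-country variances and a constant offset. The point deserves correction but does not undermine the design or the within-person comparisons.

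**What to change.** In the 6MST description, replace the claim that the stepper is identical for all participants with identical within each country. State that stepper model is confounded with country in both studies.

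Report the study 2 step-count ICC and the study 1 step-count correlations adjusted for country (or within country) alongside the pooled values. In study 1, a partial correlation keeps all 30 participants, whereas within-country values rest on 15 each.

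The cost is small: country is already known for every participant and one degree of freedom is lost. The adjusted ICC may be slightly lower. The country term removes device and country effects together, so it protects the estimates but cannot show which of the two caused a difference.

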**Standardized instructions in French**
Le but de ce test est de réaliser le plus grand nombre de pas possible pendant 6 minutes. Six minutes, c’est une longue durée, vous risquez de vous essouffler et de vous fatiguer. Vous pouvez choisir de ralentir ou d’arrêter, si nécessaire. Vous pouvez vous appuyer contre le mur pour vous reposer, mais recommencer l’exercice dès que possible.Vous devez étendre complètement la jambe pour réaliser chaque pas. Le step doit toucher la base du stepper à chaque pas. Je vais vous montrer le bon mouvement, regardez-moi. (Démonstration)Êtes-vous prêts à faire le test? L’appareil va compter le nombre de pas que vous faites et je vous dirai la durée restante toutes les minutes. Rappelez-vous, l’objectif du test est de réaliser le plus grand nombre de pas pendant 6 minutes. Je vais compter à trois et dire « GO ». Partez lorsque je dis « GO ».
**Standardized encouragements in French**
C’est bien. Il vous reste 5 minutes.Continuez comme ça. Il vous reste 4 minutes.C’est bien. Vous avez fait la moitié.Continuez comme ça. Il vous reste seulement 2 minutes.C’est bien. Il vous reste seulement 1 minute.

### Study 2: Procedures and Measurements

For study 2, in addition to a review of medical records, three 1-hour home visits (separated by 2-5 days) will be conducted. Participants will be instructed to take all medications as usual, including inhalers. Individuals who participated in study 1 will not be admissible for study 2 to reduce the risk of bias introduced by a possible learning effect with the 6MST. A summary of collected data and outcomes is presented in Table 2 and further described below.

**Table 2 table2:** Data collected during study 2.

Measurements			Medical records	Trial 1	Trial 2		Trial 3
**Sociodemographic**							
	Age	✓					
	Sex	✓					
	Pulmonary diagnosis	✓					
	Comorbidities and risk factors	✓					
**Anthropometric**							
	Mass (kg)	✓					
	Height (m)	✓					
**General lower limb function**							
	SPPB^a^ (/12)			✓			
**6MST^b^**							
	Total number of steps			✓	✓	✓	
	Dyspnea (/10)^c^			✓	✓	✓	
	Leg fatigue (/10)^c^			✓	✓	✓	
	Heart rate (bpm)			✓	✓	✓	
	Pulsed oxygen saturation (%)			✓	✓	✓	
**Adverse events**							
	Minor			✓	✓	✓	
	Serious			✓	✓	✓	
**Semistructured interview**							
	Level of comfort during test					✓	
	Perception of safety					✓	

^a^SPPB: Short Physical Performance Battery.

^b^6MST: 6-minute stepper test.

^c^/10: modified Borg Scale rating.

#### Review of Medical Records

Medical records will be reviewed, and the following information will be retrieved regarding participant sociodemographic characteristics: age, sex, pulmonary diagnosis, medications, comorbidities, and cardiovascular risk factors. Physical activity level will be assessed using the Ricci and Gagnon questionnaire [26].

#### First Trial

The first trial of the 6MST (familiarization trial) will be conducted at the participant’s home with the therapist present. Preceding this trial, the Short Physical Performance Battery will be performed to obtain a general assessment of lower limb function [39].

The 6MST will be performed using a standardized portable stepper (same as in study 1) and following the same protocol as in study 1, including the 2-minute pretest warm-up period. However, full cardiorespiratory responses will not be measured. Instead, an oximeter (Nonin) will be used to monitor heart rate and SpO_2_ continuously. Blood pressure, dyspnea, and perceived exertion will be measured pre*-* and posttest using the modified Borg scale (/10). For individuals on home oxygen therapy, oxygen flows will be titrated if SpO_2_ falls below 88% during the test, with the aim of maintaining SpO_2_ between 88% and 92%, while always respecting the flow limits of the prescribing physician’s parameters. As in study 1, the test will be terminated if blood oxygen saturation falls to ≤80% accompanied by symptoms of hypoxia (such as dizziness, nausea, etc).

All adverse events will be recorded and graded according to the Common Terminology Criteria for Adverse Events, version 5 (United States Department of Health and Human Services), progressing from mild (1) to lethal (5) [40]. Textbox 5 presents the standardized grading used in this study. Adverse events are defined as any event that leads to (or could potentially lead to) prejudice to the participant or that inhibits the completion of the test. Examples include dyspnea, dizziness or nausea, close-call or fall events, musculoskeletal pain, chest pain, syncope, etc.

Classification of adverse events based on the Common Terminology Criteria for Adverse Events, version 5.

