For objective 3, all minor and serious adverse events, for all trials, will be reported. The semistructured interviews will be voice-recorded and transcribed. Thematic content analysis will be used to analyze all verbatim [45]. Briefly, a combination of deductive (based on a priori interview guide) and inductive (based on data) approaches will be used to generate themes and subthemes. Coding will be conducted separately by 2 reviewers, who will compare their results and resolve discrepancies through discussion.

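### Study 2 does not separate the breathlessness the stepper test is expected to provoke from an adverse event, and its grading lacks a pre-test reference and specific entries for desaturation and falls

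*Protocol article*

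**What the plan says.** All of this is in the protocol article.

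- **Definition** (Study 2, First Trial). An adverse event is "any event that leads to (or could potentially lead to) prejudice to the participant or that inhibits the completion of the test". The text continues: "Examples include dyspnea, dizziness or nausea, close-call or fall events, musculoskeletal pain, chest pain, syncope, etc". Every event is to be graded by CTCAE version 5, and Textbox 5 is presented as the study's standardized grading.
- **Dyspnea grades** (Textbox 5). Grade 1 is breathlessness on moderate effort. Grade 2 is breathlessness on slight effort that restricts instrumental daily activities. Grade 3 is breathlessness at rest that restricts self-care.
- **The test** (Textbox 4). Participants are told "vous risquez de vous essouffler et de vous fatiguer", that is, that they may become breathless and tired.
- **Dyspnea as an outcome** (First Trial and Table 2). "Blood pressure, dyspnea, and perceived exertion will be measured pre"- and post-test, and dyspnea is listed for all three trials.
- **Saturation.** Oximetry is continuous, and Table 2 lists "Pulsed oxygen saturation" at each trial. In addition, "the test will be terminated if blood oxygen saturation falls to ≤80% accompanied by symptoms of hypoxia".
- **Population.** GOLD 2 to 4 COPD or ILD. Study 2 admits oxygen users: "For individuals on home oxygen therapy, oxygen flows will be titrated" below an SpO2 of 88%.
- **Hypothesis and reporting.** Objective 3 calls the test safe if there are no serious adverse events. The analysis section says "all minor and serious adverse events, for all trials, will be reported".

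**The concern.** A safety count is useful when it records something other than the intended effect of the procedure. Here breathlessness is both a scheduled response and the first named harm, and the text gives no rule for telling them apart. Two therapists could watch the same ordinary test, one logging a Grade 1 event and the other nothing, and both could defend it from the text.

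The dyspnea grades compound this because they describe how limited a person is, not how much worse the person has become. Some participants may fit the Grade 2 or Grade 3 description before they step.

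Meanwhile, the risks most particular to stepping at home have no specific line in the study's own grading box. At stake are the minor-event result of objective 3 and, to a lesser degree, the consistency of grading near the point where an event might be called serious.

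**Working it through.** No figure in the plan needs to be reproduced for this point. The check is mainly textual, with simple arithmetic for scale.

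**Step 1: set the named risks against Textbox 5.**

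| Risk | Named as an example (First Trial) | Specific entry in Textbox 5 | Captured elsewhere |
|---|---|---|---|
| Dyspnea | yes | Grades 1 to 5 | Borg rating at every trial |
| Dizziness or nausea | yes | none | symptoms within the termination rule |
| Close call or fall | yes | none (musculoskeletal injury: Grades 1 to 3) | balance problems foreseen under Potential Challenges |
| Musculoskeletal pain | yes | Grades 1 to 3 | no |
| Chest pain | yes | Grade 2 | no |
| Syncope | yes | Grade 3 | no |
| Desaturation | no | none | oximetry, Table 2, termination rule |

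Two of the six example groups have no specific entry. Desaturation is in neither list, although with symptoms it is the stated ground for ending a 6MST in study 2.

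**Step 2: apply the general definitions to the unlisted events.** Each grade opens with a general definition, so unlisted events can be graded, but not always to a single answer.

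- Desaturation managed with oxygen fits Grade 2 if oxygen is a noninvasive intervention. By analogy with the wheezing entry, where a need for oxygen means Grade 3, it fits Grade 3.
- A close call without symptoms falls to Grade 1 and is pooled with ordinary breathlessness.

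Objective 3, Table 2 and the analysis section speak of minor and serious events. The text shown does not tie those words to Grades 1 to 5, so a choice between Grades 2 and 3 could matter to the hypothesis.

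**Step 3: look for a pre-test reference.** None of the Grade 1 to 3 dyspnea entries mentions change from the state before the trial. The comparison would be possible, because dyspnea is rated before each test.

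**Step 4: scale.** Study 2 recruits 52 people with three tests each: 52 × 3 = 156 tests. The documents do not say how often therapists would log exertional dyspnea. Assuming at most one such event per test:

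- 25%: 0.25 × 156 = 39 events
- 50%: 0.50 × 156 = 78 events
- 90%: 0.90 × 156 = 140.4, about 140 events

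With the planned 15% dropout, 52 × 0.85 = 44.2, so about 44 people and 44 × 3 = 132 tests. The same rates give 33, 66 and about 119 events.

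**Step 5: inconsistent logging.** Each country contributes 26 people, or 26 × 3 = 78 tests. Suppose 90% of tests end with breathlessness, one country logs all of them and the other none. The counts would be 0.90 × 78 = 70.2, about 70, against 0 with no difference in safety. This is an extreme illustration, not a forecast.

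**The case against.** The strongest reply is that the grading is not closed. All events are graded under CTCAE, every grade has a general definition, and the Textbox 5 lists are introduced as illustrations. Falls and close calls are named as events to record, SpO2 is measured at every trial, and a test stopped for desaturation meets the part of the definition about not completing the test. A reader might infer from the missing entries that these risks receive no grade or could vanish from the report. The documents do not support that. What remains is that they lack a specific entry, and that the general definitions leave desaturation open between two grades.

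Second, the definition requires actual or potential harm, or a test that cannot be completed, so ordinary breathlessness in a completed test need not qualify. That reading is reasonable, but the text does not impose it: dyspnea is the first example and its Grade 1 entry describes ordinary exertion. Since both readings are open, inconsistent logging is a real prospect. Inclusive capture is defensible for a safety objective, but only if expected responses can be told apart afterwards.

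Third, nothing directs staff to grade pre-existing disability, participants must be clinically stable for at least 4 weeks, and signs of exacerbation are checked before repeated home tests. This stands: the misgrading is an inference about what the wording permits, not something it orders.

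Fourth, safety is defined by the absence of serious events, which Grade 1 dyspnea would not normally affect. This also stands, and it limits the point mainly to the minor-event count.

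**Conclusion.** The point holds in a limited form. The definition and Textbox 5 do not separate expected exertional dyspnea from an adverse event, the dyspnea grades have no pre-test reference, and desaturation, falls or close calls, and dizziness or nausea lack specific entries. This goes beyond detail left to a fuller document, because the stated rule itself makes the minor-event count poorly informative.

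The size is not known from the documents. The range of about 39 to 140 events over 156 tests rests on assumed logging rates of 25% to 90%. A reader might infer that practically every test would carry an event, but that would need universal breathlessness and universal logging, and neither is stated.

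A reader might also infer that direct and remote trials could not be compared. That goes too far: the same definition applies in both modes, within the same people, and the plan promises only to report events. Minor-event counts would simply say little about either mode. The serious-event hypothesis is affected only where the choice between Grades 2 and 3 is ambiguous.

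**What to change.** Settle this before study 2 starts. Its recruitment follows study 1, so the schedule leaves room.

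1. **Grade change, not state.** Grade each event as a worsening from the status recorded before that trial. Keep ordinary exertional dyspnea and leg fatigue as Borg outcomes. Count dyspnea as an adverse event only if it ends the test or is still above its pre-test rating at a fixed post-test time. Study 1 describes a rating 5 minutes after the test, whereas the study 2 text says only post-test, so the time must be stated.
2. **Add the missing entries.** Give desaturation and falls or close calls their own lines in Textbox 5. The sponsor's clinical team should set the grades so that the wheezing entry and the general Grade 2 definition no longer point in different directions for oxygen use.
3. **Report what is already monitored.** By supervision mode, give the number of tests with SpO2 below 88%, with SpO2 at or below 80% (with and without symptoms), and ended early. Both thresholds are the protocol's own.

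No stopping or oxygen rule changes. The cost is rewording Textbox 5 and the case report form, keeping each test's lowest SpO2 if it is not already stored, and fixing the post-test rating time. Expected dyspnea leaves the minor-event total but remains reported as a Borg outcome.
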